Both genetic predisposition and intervention difference between individuals affect the clinical outcomes of patients (6, 22). To increase the statistical potency of the therapeutic effect of cord blood stem cells especially among small sample trials, enrolling very preterm monozygotic twins of less than 32 gestation weeks (GW) could improve the comparability between intervention and control groups as the hereditary material is the same within monozygotic twins.

With these concepts in mind, here, the authors will enroll very preterm monozygotic twins and assign the random number. Therefore, one of the twins will be assigned to the control group and the other to the intervention group. Furthermore, we will perform single-cell RNA sequencing for cord blood cells and blood cells 3–10 days after intervention and detect whether reactive oxygen species and inflammatory cytokines are present in serum from abandoned blood samples. As the genetic background is the same within monozygotic twins, the results of single-cell RNA sequencing are expected to have better comparability, following which the mechanisms elucidated will reveal the effect of autologous cord blood mononuclear cell (ACBMNC) infusion to the maximum (23). This will be the first randomized, placebo-controlled, and double-blinded trial to evaluate the efficacy of ACBMNC infusion as a prophylactic measure for BPD in monozygotic twin premature infants who have the same genetic background and investigate the underlying protective mechanisms *via* single-cell RNA sequencing.

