### Sample size

Our previous study showed that ACBMNC infusion was effective in reducing respiratory support duration in preterm infants (18). A randomized study in Korea by Won Soon Park showed that severe BPD incidence significantly reduced from 53% to 19% with mesenchymal stem cell intervention in the 23–24 GW group (*n* = 33) (20). The rate of BPD among very preterm infants at our NICU was 30% (pA), which is similar to the incidence rate reported previously (26). The sample size of this study was determined for assessing the efficacy of ACBMNCs compared with placebo with respect to the primary outcome in order to decrease the incidence of BPD or death with a two-sided α level of 0.05% and 80% power. We expect the intended (or at least acceptable) effect of ACBMNC infusion to be at a rate of 20% decrease in the frequency of BPD. To achieve this rate, at least 60 patients per group will be required based on the following formula:n=(pA(1−pA)/κ+pB(1−pB))((z1−α/2+z1−β)/(pA−pB))2)

κ = nA/nB is the matching ratio; α is type I error; β is type II error, meaning 1 − β is power.

Around 20 pairs of monozygotic twin births of less than 32 gestational weeks occur annually in Guangdong Women and Children Hospital and Dongguan Maternal and Child Health Hospital. Around 6 pairs of monozygotic twin births of less than 32 gestational weeks take place annually in Zhongshan Boai Hospital, Shunde Hospital, Southern Medical University, Dongguan Hospital, Southern Medical University, Nanfang Hospital, Southern Medical University, and Affiliated Maternal and Child Hospital of Foshan, Southern Medical University. Therefore, we assume that 60 pairs of monozygotic twins will be enrolled annually and the trial could be completed within 1 year.

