### Safety monitoring and co-intervention

Assessment of safety is conducted before, during, and 12 and 24 h after infusion. The heart rate, systolic, diastolic, and mean arterial blood pressure, and arterial blood oxygen saturation level are monitored continually and documented; these are also monitored during the period of hospitalization and return visits. The levels of arterial blood gas and blood glucose in peripheral blood are monitored and kept stable during the whole treatment period. Infusion reactions (fever, hemolysis, hyperbilirubinemia, and urine color changes) and signs of circulatory overload (tachycardia, dyspnea, edema, and hepatomegaly) are observed and checked during infusion and 48 h after infusion.

The trial will be strictly monitored by the members of a safety monitoring board comprising an ethics committee member, project principal, good clinical practice member, and statisticians, and they will be notified of any severe adverse events (including death, LOS, NEC, severe IVH, and cystic periventricular leukomalacia). Other adverse or unexpected events will be reviewed immediately after they are discovered. After each interim analysis (every 3 months), the data safety monitoring board will make a decision on whether to stop or continue the trial based on safety monitoring and sequential analysis of the primary outcome.

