### Outcome measures

Primary outcome:
– Surviving without BPD.Secondary outcomes:
– Surviving without severe preterm-associated complications (severe BPD, severe ROP, and severe IVH).– Mortality rate.– BPD severity.Other outcomes:
– Incidence of other preterm complications including IVH, PVL, NEC, ROP, RDS, VAP, LOS, and anemia.– Duration of mechanical ventilation and oxygen therapy.– Frequency of re-intubation.– The time (days) to return to BW.– Body weight during the first 4 weeks (measured on each week).– Duration of hospitalization.– Hospitalization expenses.We will use the following clinical definitions in this study: (all clinical diagnoses will be defined according to a standard reference) (30).
1.GA will be determined on the basis of a combination of the last menstrual period and early ultrasound findings.2.The diagnosis of common preterm complications will include the following:

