### Follow-up

All infants will be followed up three times (corrected GA of 40 weeks and corrected age of 12 and 24 months), and the following parameters will be recorded.

*Follow-up content at corrected GA of 40 weeks:*
– Main caregiver and the education level.– Smoking in main caregivers.– Feeding mode (breastfeeding, formula, and mixed feeding).– Anthropometric characteristics: weight, length, and head circumference.– Respiratory outcomes: the occurrence of wheezing, supplemental oxygen requirement, and rehospitalization because of pneumonia.– Neurodevelopmental outcome: neonatal behavioral neurological assessment score, the occurrence of seizure, encephalomalacia, intracranial hemorrhage, and auditory and visual impairment.– Results of blood routine examination.*Follow-up content on corrected age of 12 and 24 months:*
– Anthropometric characteristics: weight, length, head circumference, and anterior fontanel size.– Respiratory outcomes: the occurrence of wheezing, asthma, nocturnal cough, supplemental oxygen requirement, and rehospitalization because of pneumonia.– Degree of neurodevelopmental impairment *via* standardized neurological examination (using the Bayley scales) and other major neurodevelopmental outcomes such as cerebral palsy, seizures, auditory impairment, and visual impairment.– Results of blood routine examination.

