### Statistical analysis

Mean and standard deviation are reported for continuous variables, and the number and percentage are reported for categorical variables. Group comparisons of categorical variables for outcomes and co-interventions including death, BPD, and BPD severity are performed using nonparametric tests, the Fisher's exact test, or chi-square test, as appropriate. The relative risk (RR) is calculated as the ratio of the cumulative incidence rates of an event occurring in the intervention infusion group to the control group, and the number needed for treatment as the inverse of these two cumulative incidence rates. The results are shown as RR with 95% confidence interval (CI). For continuous variables, the mean values at each time point in each group of the variables are derived from a generalized linear model and the differences in the values over time are compared using an unpaired Student's t-test between the two groups. Kaplan–Meier cumulative incidence plots are generated to show time-to-event end points, namely, extubation and weaning to room air. All statistical tests are two-tailed, and *p*-values < 0.05 are deemed statistically significant. The Breslow–Day test and Cochran–Mantel–Haenszel (CMH) test will be used to adjust the data derived from different participating centers. The results will be reported as odds ratio (OR) with 95% CI. All statistical tests will be two-tailed and a *p*-value < 0.05 will be considered statistically significant. All statistical analysis will be performed using SPSS 21.0 (IBM).

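### Change over time in continuous outcomes is tested with an unpaired t-test although each twin pair is split across the arms, so the standard error is too large whenever twins change alike

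*Protocol article*

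**What the plan says.** In the protocol article, Statistical analysis gives two procedures for continuous variables. First, "the mean values at each time point in each group of the variables are derived from a generalized linear model". Second, "the differences in the values over time are compared using an unpaired" Student's t-test, applied between the arms. It names no twin-pair term, no infant term and no repeated-measures covariance.

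Several continuous variables are measured more than once on each infant. Outcome measures lists, among the other outcomes, "Body weight during the first 4 weeks (measured on each week". Follow-up states "All infants will be followed up three times (corrected GA of 40 weeks and corrected age of 12 and 24 months", with weight, length and head circumference at each visit. Safety monitoring and co-intervention adds serial vital signs: "Assessment of safety is conducted before, during, and 12 and 24 h after infusion".

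On allocation, the Introduction says that "one of the twins will be assigned to the control group and the other to the intervention group". Study design and settings and Randomization describe the same rule: one random number per pair fixes both infants' arms. The Discussion argues that this design raises statistical power and lowers the sample size needed.

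**The concern.** An unpaired t-test assumes that the two groups are independent samples. Here every infant in one arm has a monozygotic twin in the other, with the same genes, gestation and centre. If the twins' changes are positively correlated, the between-arm difference is more precise than the unpaired formula reports. Confidence intervals are too wide, p-values are too large, and a real difference in growth or in a serially measured safety variable is easier to miss.

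There is also a mismatch within the sentence. The means come from one analysis and the p-value from another, so no single analysis gives the mean, the difference, its interval and its test. Nor does the text say whether the differences over time are changes computed for each infant or contrasts of the model means.

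**Working it through.** **The plan's own figure.** The documents give no number for the continuous analysis. The only design figure is 60 per group for the binary primary outcome. With the article's formula, 30% against 10%, two-sided α of 0.05 and 80% power:

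n = (0.30×0.70 + 0.10×0.90) × ((1.960 + 0.842)/0.20)² = 0.30 × 196.2 = 58.9, so 59 against the stated 60.

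That agrees, provided that α is 0.05. The text prints "with a two-sided α level of 0.05% and 80% power", and a literal 0.0005 would give 141. The formula is for independent groups and has no bearing on the continuous outcomes, except that it sets 60 pairs.

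**Effect of ignoring the pair.** Let each infant have one change score with variance s², let ρ be the correlation of that change between twins, and let n be the number of pairs.

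- True variance of the between-arm difference: 2s²(1 − ρ)/n
- Variance used by the unpaired test: 2s²/n
- Standard error, unpaired over true: 1/√(1 − ρ)
- Actual type I error: 2 × [1 − Φ(1.96/√(1 − ρ))]

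For power, take an effect that an unpaired test would detect with 80% power if twins were uncorrelated. It equals 2.80 unpaired standard errors (1.96 + 0.84). Power is then Φ(0.84/√(1 − ρ)) for the unpaired test and Φ(2.80/√(1 − ρ) − 1.96) for the paired test.

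| ρ (assumed) | SE ratio | Type I error, unpaired | Power, unpaired | Power, paired |
|---|---|---|---|---|
| 0 | 1.00 | 0.05 | 0.80 | 0.80 |
| 0.3 | 1.20 | 0.019 | 0.843 | 0.918 |
| 0.5 | 1.41 | 0.006 | 0.883 | 0.977 |
| 0.7 | 1.83 | 0.0003 | 0.938 | 0.999 |

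A simulation (60 pairs, 5 visits, equal correlation between visits, 3,000 runs per setting) agrees. At ρ = 0.5 the unpaired test of change has type I error 0.005 to 0.007, and the paired test 0.045 to 0.052.

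**Effect of correlation between visits of one infant.** Let r be that correlation and σ² the variance of a single value. A change has true variance 2σ²(1 − r). A t-test on per-infant changes estimates this directly from the observed changes. In the same simulation with ρ = 0, its type I error was 0.048 to 0.054 for r from 0.3 to 0.9, so r does no harm. An analysis that treated visits as independent rows would use 2σ² instead, which is too wide for a change. For a level pooled over visits it would be too narrow.

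**The case against.** **Serial correlation.** A reader might infer that, because the generalized linear model has no infant term, every test of change over time has wrong error bars, with many false positives or a collapse in power. The documents do not support that. The model is assigned only the means, and the test is a t-test between the two groups. The natural reading is one change score per infant, and subtraction already deals with correlation between that infant's visits. No test pooled over visits, and none using the model's own standard errors, is stated.

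**Omission.** An article may leave the covariance structure to the full protocol or analysis plan. That stands for the within-infant covariance, which is therefore only a matter to clarify. It does not cover the word unpaired, which the article states outright.

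**Meaning of unpaired.** The word may be meant only to separate a between-group test from a before-and-after test. That is plausible, but the two groups are matched by design and the test named takes no account of it.

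**Direction.** With positively correlated twins the error is conservative, so it does not create false positives. That is true. Some of the benefit of matching also survives, because power under the unpaired test still rises with ρ. But most of the gain is lost (0.883 against 0.977 at ρ = 0.5), and for safety variables a conservative test is no protection.

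**Size.** Subtraction removes any stable level that twins share, so ρ for change may be lower than for single values. This stands and is why a range is shown.

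**Conclusion.** The point holds as a fault in how the named test treats twin pairs. The unpaired test contradicts the matched design. For assumed twin correlations in the change of 0.3 to 0.7, its standard error is 1.20 to 1.83 times too large and its type I error 0.019 down to 0.0003. At ρ = 0 there would be no error, and a negative correlation would reverse its direction. The figures assume complete pairs and equal variance in the arms.

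The split between the model for the means and the test for the p-value is a second, smaller defect that holds under any reading. Distortion from correlation within an infant is possible but not established.

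The reach is limited to continuous variables under the other, safety and follow-up outcomes. The article does not explicitly assign the t-test to the infusion vital signs, so they are affected only if the general sentence is applied to them. The binary primary outcome and the sample size are untouched by this point.

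**What to change.** Replace the sentence on continuous variables with one linear mixed model per repeated variable:

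- fixed effects for arm, visit (categorical) and arm-by-visit;
- twin pair as a random effect, allowed to vary by visit, because a constant pair effect cancels out of any change and would not capture ρ;
- a within-infant covariance across visits.

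Take the group means, between-arm differences, 95% confidence intervals and the overall arm-by-visit test from that model, and drop the separate t-test for these variables. Where a single change score is the measure, say that it is computed per infant and compare it by a paired analysis of within-pair differences. The mixed model has the advantage of keeping an infant whose twin has no value.

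The cost is a rewritten sentence and slightly more analysis work. The SPSS version already named has a mixed-model procedure, and no new data are needed.

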**Methods:**

In this prospective, randomized, placebo-controlled, double-blinded multicenter clinical trial, 60 pairs of monozygotic twin preterm neonates of less than 32 weeks admitted to the Neonatal Intensive Care Unit are randomly assigned to receive intravenous ACBMNC infusion (targeted at 5 × 10^7^ cells/kg) or placebo (normal saline) within 24 h after birth in a 1:1 ratio. The primary outcome will be survival without BPD at 36 weeks of postmenstrual age. The secondary outcomes will include the mortality rate, BPD severity, other common preterm complication rates, respiratory support duration, length and cost of hospitalization, and long-term respiratory and neurodevelopmental outcomes during a 2-year follow-up. Furthermore, we will perform single-cell RNA sequencing for cord blood cells and blood cells 3–10 days after intervention and detect whether reactive oxygen species and inflammatory cytokines are present.

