### Secondary objectives

The secondary objectives of this trial are as follows: (1) to compare the infant mortality rate at 36 weeks of postmenstrual age; (2) to compare the rates of other common preterm complications such as intraventricular hemorrhage (IVH), necrotizing enterocolitis (NEC), retinopathy of prematurity (ROP), respiratory distress syndrome (RDS), ventilation-associated pneumonia (VAP), hypoxic ischemic encephalopathy (HIE), late-onset sepsis (LOS), periventricular leukomalacia (PVL), and anemia; (3) to compare the duration of mechanical ventilation and oxygen therapy in the two groups; (4) to determine the re-intubation rate and time of return to birth weight (BW); (5) to compare the duration of antibiotic usage; (6) to determine the long-term outcomes during a 2-year follow-up, including anthropometric characteristics, respiratory outcomes, and neurodevelopmental outcomes *via* a standardized neurological examination; (7) to compare the results of single-cell RNA sequencing for cord blood cells and blood cells 3–10 days after intervention and detect whether reactive oxygen species and inflammatory cytokines are present in serum.

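### The plan names Kaplan–Meier for the cumulative incidence of extubation and weaning, which death precludes, and gives no rule for deaths in these curves or in mean durations of support (minor)

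*Protocol article*

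**What the plan says.** The Statistical analysis section chooses the estimator itself: "Kaplan–Meier cumulative incidence plots are generated to show time-to-event end points, namely, extubation and weaning to room air". For continuous variables it derives means at each time point from a generalized linear model and adds that "the differences in the values over time are compared using an unpaired Student's t-test between the two groups".

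Durations of respiratory support are outcomes. Secondary objective (3) is "to compare the duration of mechanical ventilation and oxygen therapy in the two groups". The Outcome measures section lists "Duration of mechanical ventilation and oxygen therapy" and length of hospital stay under other outcomes.

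Death is an outcome too. The Abstract says "The primary outcome will be survival without BPD at 36 weeks of postmenstrual age", the first secondary objective is "to compare the infant mortality rate at 36 weeks of postmenstrual age", and Outcome measures lists mortality among the secondary outcomes. The Exclusion criteria remove infants expected to die within 24 hours, so later deaths stay in the trial.

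Nowhere does the protocol say how an infant who dies before extubation or weaning enters the curves or the mean durations. It gives no expected mortality.

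**The concern.** Kaplan–Meier with deaths censored estimates the proportion who would have weaned by a given day if nobody could die. That is not cumulative incidence, which is the proportion of enrolled infants who actually weaned. A curve labelled as cumulative incidence would then read too high, and by more as mortality rises.

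Durations raise a similar question. Death ends time on support, so if the days up to death are entered as an ordinary value, an early death counts as a short and apparently favourable duration.

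At stake are the respiratory-support results. They are not primary, but they are likely to be cited: the Sample size section opens by citing a previous study by the same group that reported shorter respiratory support after the same type of infusion.

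**Working it through.** **The plan's own figure.** The plan states no figure for these analyses. Its one calculation is the sample size. The printed formula with pA = 0.30 ("The rate of BPD among very preterm infants at our NICU was 30% (pA"), pB = 0.10 (taking "at a rate of 20% decrease in the frequency of BPD" as 20 percentage points), two-sided α = 0.05 and 80% power gives

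n = (0.30×0.70 + 0.10×0.90) × ((1.960 + 0.842)/0.20)² = 58.87, so 59 against the stated 60.

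The formula contains no time-to-event or duration input, so the number does not depend on this point.

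**Step 1: error of a single curve.** Assume constant hazards of weaning (λ₁) and death (λ₂) up to a 60-day horizon τ. Let C be the true cumulative incidence of weaning, m the proportion dying before weaning, and T = C + m. Then

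- T = 1 − exp(−(λ₁+λ₂)τ) and λ₁τ = −ln(1−T) × C/T;
- with deaths censored, 1−KM = 1 − exp(−λ₁τ) = 1 − (1−T)^(C/T).

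Example with C = 0.80 and m = 0.10: 1 − 0.10^(0.889) = 0.871, an overstatement of 7.1 points.

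| Assumed mortality | 1−KM when truth is 80% | Overstatement (truth 80%) | Overstatement (truth 70%) |
|---|---|---|---|
| 2% | 81.2% | 1.2 | 1.0 |
| 5% | 83.2% | 3.2 | 2.6 |
| 10% | 87.1% | 7.1 | 5.5 |
| 15% | 92.0% | 12.0 | 9.0 |

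A simulation with a different shape agrees. Weaning times were lognormal (median 30 days, σ 0.7), with deaths spread evenly over days 1–28 and unrelated to weaning time. At day 70, 1−KM is 88.7%. The true proportion weaned is 85.1%, 81.6% and 78.0% at mortality of 5%, 10% and 15%, so the overstatement is 3.6, 7.1 and 10.7 points.

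**Step 2: comparison between arms.** Give both arms the same weaning hazard, so that 1−KM is 80% in each (λ₁τ = −ln 0.20 = 1.609). Solve for λ₂ at each mortality, and take C = λ₁/(λ₁+λ₂) × (1 − exp(−(λ₁+λ₂)τ)).

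- Equal mortality: the true incidences are equal and the comparison shows no artefact.
- 10% v 5%: true incidence 73.9% v 77.0%. The curves coincide and hide 3.1 points.
- 15% v 5%: 70.8% v 77.0%. They hide 6.2 points.

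**Step 3: durations.** Let survivors average D days on support and let deaths occur at day d, entered as d days. With no treatment effect among survivors, the difference in means is (difference in mortality) × (D − d). Assume D of 20–40 days and d of 5–10 days.

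- 10% v 5%: from 0.05 × (20 − 10) = 0.5 to 0.05 × (40 − 5) = 1.75 days, with the higher-mortality arm looking shorter.
- 15% v 5%: 1.0 to 3.5 days.
- Equal mortality: zero.

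**The case against.** The case for leaving the text alone has four parts.

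- **Censoring at death is not written down.** If infants who die were kept at risk to the end of the window, Kaplan–Meier would equal the cumulative incidence. This is correct and makes the point conditional. But the protocol does not say so, and censoring at death is standard use.
- **The curves are plots.** No log-rank or Cox analysis is named, and Outcome measures places durations under other outcomes. This stands and limits the severity.
- **The t-test sentence concerns values over time**, which fits serial measurements such as weekly weight. Durations are not named there and come under it only as continuous variables. This stands, so the duration part must stay conditional.
- **Handling of deaths may sit in an analysis plan that is not shown.** That is fair for durations. It does not rescue the curves, because the estimator is chosen in the protocol.

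A reader might also infer more than the documents support.

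- *That Kaplan–Meier makes the higher-mortality arm look faster to wean.* When death is unrelated to weaning time, 1−KM is 88.7% at every mortality in the simulation, so it hides a difference and does not reverse one. If slower-weaning infants are the ones who die, 1−KM does drift upward (88.8% to 90.0% as mortality goes from 2% to 15%, in a run that assumed this), but nothing in the protocol establishes that pattern.
- *That death makes up half of the primary outcome.* It is one of two components. No share of events is given, and the 30% is stated for BPD. If deaths add to that 30%, assumed mortality of 2–15% makes death 6–33% of failures (0.02/0.32 to 0.15/0.45).
- *That BPD severity is compared only among survivors.* The protocol does not say where deaths go in that comparison.

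**Conclusion.** The point holds in a limited form, and its severity is minor. The protocol names an estimator that, used in the standard way, does not give the cumulative incidence it is said to show.

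The overstatement of a single curve is about 1 point at 2% mortality, 3–4 at 5%, 6–7 at 10% and 9–12 at 15%. Misleading comparison between arms needs unequal mortality or deaths concentrated among slow weaners. With unequal mortality alone, about 3 points are hidden at 10% v 5%.

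The duration distortion, 0.5–1.75 days at 10% v 5%, rests on three conditions: durations are compared as means, deaths enter as short durations, and mortality differs between arms.

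All mortality rates, weaning times and days of death above are assumptions, since the protocol supplies none. The primary outcome already counts death, and neither it nor the sample size changes.

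**What to change.** In the Statistical analysis section:

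- Replace Kaplan–Meier for extubation and weaning to room air by Aalen–Johansen cumulative incidence, with death as a competing event and a variance that accounts for the twin pairs.
- Report ventilation and oxygen as days alive and free of that support to 36 weeks of postmenstrual age, with death scored as zero free days. Compare within pair, for example by a signed-rank test on the within-pair differences. Twins share a gestational age, so both members of a pair have the same window.
- State a rule for deaths in length of stay if it remains a comparison of means.

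No new data are needed. The cost is revised wording, a few lines of analysis code, and one sentence explaining that free days combine survival with time off support. Mortality is already reported separately, so a reader can see what drives the composite.

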### Exclusion criteria

Infants will be excluded from the study if (1) they exhibit severe congenital abnormalities (detected *via* prenatal ultrasound); (2) their condition is critical and are expected to die within the first 24 h; (3) they are diagnosed with twin-to-twin transfusion syndrome confirmed by prenatal ultrasonography (24).

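### Kaplan–Meier is named for extubation and weaning to room air with no method for death as a competing event, so on the usual reading the two plots overstate recovery in any arm with deaths first

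*Protocol article*

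**What the plan says.** The Statistical analysis section of the protocol article fixes one estimator for two endpoints: "Kaplan–Meier cumulative incidence plots are generated to show time-to-event end points, namely, extubation and weaning to room air". It does not say how an infant who dies before the event enters the curve, and no section names a competing-risk method. The same section gives SPSS 21.0 as the only software.

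Death is provided for elsewhere:
- The abstract's Methods state: "The primary outcome will be survival without BPD at 36 weeks of postmenstrual age".
- The first secondary objective is "to compare the infant mortality rate at 36 weeks of postmenstrual age", and "Mortality rate" is listed as a secondary outcome under Outcome measures.
- Death has its own comparison between arms: "Group comparisons of categorical variables for outcomes and co-interventions including death, BPD, and BPD severity are performed using nonparametric tests", with Fisher's exact or the chi-square test as alternatives.
- The exclusion criteria remove infants if "their condition is critical and are expected to die within the first 24 h". Infants who die later stay in the trial.

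No log-rank test, hazard ratio or decision rule is given for extubation or weaning. The nearest listed outcomes, the durations of mechanical ventilation and oxygen therapy, stand under other outcomes.

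**The concern.** Extubation and weaning are favourable events that death rules out. A Kaplan–Meier curve that censors a death assumes that the infant would later have come off support at the rate of the infants still at risk. One minus that curve estimates what would happen if nobody died. It is not the proportion who came off support alive, which is what a reader takes a cumulative incidence plot to show.

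The error has one direction: too high wherever deaths precede the event, and larger where more infants die. If the infusion changed mortality, the two arms' curves would be inflated by different amounts, and the gap between them would not be the gap in infants who recovered. These are the only time-to-event displays of respiratory recovery that the article plans.

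**Working it through.** **A figure to reproduce.** The article states none for extubation or weaning. Its sample size concerns the primary outcome and has no bearing here.

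**Inputs.** The article gives neither a mortality rate nor a time to extubation or weaning, so everything below is assumed. Hazards are constant, and *q* is the share who would eventually die before the event. Two settings are used: A, median time to event 10 days, read at day 56; B, median 28 days, read at day 70.

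**Formulas.**
- Event hazard: λ = ln 2 / median.
- Death hazard: μ = λq/(1 − q), so that μ/(λ + μ) = q and λ + μ = λ/(1 − q).
- One minus Kaplan–Meier with deaths censored: 1 − exp(−λT). It does not depend on *q*.
- True cumulative incidence: (1 − q) × [1 − exp(−λT/(1 − q))].

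**Setting A.** λ = 0.0693 per day and λT = 3.882, so one minus Kaplan–Meier is 1 − exp(−3.882) = 97.9%. For q = 5%: 3.882/0.95 = 4.086, and 0.95 × (1 − 0.0168) = 93.4%.

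**Setting B.** λ = 0.0248 per day and λT = 1.733, so one minus Kaplan–Meier is 1 − exp(−1.733) = 82.3%. For q = 5%: 1.733/0.95 = 1.824, and 0.95 × (1 − 0.161) = 79.7%.

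The other rows follow in the same way. Differences are taken before rounding.

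| Dying first (q) | A: true incidence | A: excess of 97.9% | B: true incidence | B: excess of 82.3% |
|---|---|---|---|---|
| 5% | 93.4% | 4.5 points | 79.7% | 2.7 points |
| 10% | 88.8% | 9.1 points | 76.9% | 5.4 points |
| 15% | 84.1% | 13.8 points | 73.9% | 8.4 points |

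**Sensitivity.** At 2% dying first, the excess in setting B is 1.0 point. With a 7-day median read at day 70, it is almost the whole share who die: 2.0 points at 2% and 19.9 points at 20%.

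**Simulation.** With 60 infants per arm and 4,000 runs in setting B, the Kaplan–Meier and true figures were 82.3% and 79.7% at 5% dying first, and 82.4% and 77.0% at 10%. The true figure here is the simple proportion weaned by day 70. A Kaplan–Meier routine also returns it if infants who die are kept at risk to day 70 and nobody else is censored.

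**Between arms.** Take equal event hazards, with 5% dying first in one arm and 15% in the other. One minus Kaplan–Meier is identical in both arms, a difference of 0. The true incidences differ by 93.4 − 84.1 = 9.3 points in setting A and by 5.7 points in setting B.

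**The case against.** **Censoring at death is an inference.** A reader might take the article to say that infants who die are censored. It does not. If they are kept at risk to a common end day and nobody else is censored, the Kaplan–Meier routine gives the correct cumulative incidence. This stands. But censoring is the ordinary reading of the method named, and the alternative departs from it in a way that would need to be stated.

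**No survival difference is hidden in the trial.** A reader might infer that a mortality effect would go unseen. The article does not support that: death is a failure in the primary outcome, and mortality is a secondary outcome with its own comparison. A difference would be missing from these two plots only.

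**Frequency of death is unknown.** Death being part of the primary outcome does not show that it is common, since it would belong there at any frequency because it precludes survival without BPD. The eligibility criteria also remove several high-risk groups. At 2% dying first, the bias in setting B is 1 point. This stands, and the size must be read as a range.

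**Definitions of risk set and event.** One could add that never-intubated infants have no stated place in the extubation curve, and that with "Frequency of re-intubation" as an outcome it is unclear which extubation counts. A journal article may leave such details to the full plan, and the text does not restrict the curve to intubated infants. Neither is counted here.

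**Status of the plots.** They carry no test, and no primary or secondary conclusion rests on them. This stands and sets the severity.

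**Conclusion.** The concern holds in a limited form. The article names an estimator that, as usually applied, does not give a cumulative incidence when death can come first, and it says nothing to change that reading. The direction is certain in any arm with deaths before the event, provided deaths are censored. The size cannot be fixed from the document. With constant hazards and medians of 28 to 10 days, it is about 3 to 5 points at 5% dying first and 5 to 9 points at 10%. With 5% versus 15% dying and equal event hazards, the plots would show no difference where the true one is about 6 to 9 points.

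Severity is minor. Two descriptive displays of non-primary endpoints are affected. The primary analysis and the mortality comparison are not.

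**What to change.** In the Statistical analysis section, replace Kaplan–Meier for these two endpoints by the Aalen–Johansen cumulative incidence function, with death as the competing event, and plot the cumulative incidence of death alongside for each arm.

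Alternatively, keep infants who die in the risk set to a stated common end day instead of censoring them at death. The ordinary Kaplan–Meier routine in the named software can then be used. This is valid only if there is no other censoring before that day. The condition needs checking for infants who go home on oxygen: Clinical data collection lists support mode in the first 28 days, at 36 weeks and at discharge, and support duration, but no exact date of weaning after discharge.

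The cost is one or two sentences. Deaths and support durations are already needed for the listed outcomes. The sample size and the primary analysis do not change.
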